### Objectives

Our primary objective is to demonstrate the superiority of the intensified short course (6 months) ATT regimen containing high-dose rifampicin and moxifloxacin and standard ATT regimen (12 months) in reducing composite outcome of mortality or disability among adults with TBM. Secondary objectives are to assess the safety and tolerability of high-dose rifampicin and moxifloxacin when given daily for 8 weeks and pyrazinamide administration for 6 months. We also aim to compare the pharmacokinetic (PK) parameters of ATT in the serum and cerebrospinal fluid (CSF) between the three arms, and to compare the health-related quality of life between the intervention and control arms.

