### Randomization

Computer generated list of random numbers using permuted block randomization will be created and uploaded in RedCap data base.When all the screening results are available and within the normal range, the patient will be randomly allocated in a ratio of 1:1:1 to one of the treatment groups. The study sites will be required to ensure inclusion and exclusion criteria for each patient prior to enrolment and enter the data in the baseline case report form with the eligibility criteria in RedCap data base. Upon verification of the case report form and the eligibility criteria, the ICMR-NIRT statisticians (randomization team) will approve for randomization and site investigators can proceed for online randomization in Redcap.

 Allocation concealment will be ensured, as the randomization team will not approve the randomization until the patient has been recruited into the trial, which takes place after all baseline assessments are completed. The intervention will be administered by the site investigators who will also be treating physicians.

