#### Arm 3 (control arm)

The control arm will receive treatment according to the standard national guidelines for TBM. They will receive a first-line regimen consisting of 2 months of isoniazid, rifampicin, ethambutol, and pyrazinamide followed by 10 months of isoniazid, rifampicin, and ethambutol daily in a fixed-dose combination (FDC) as per the various weight bands in National TB Elimination Programme of India. Participants will also receive steroids as in the other two arms.

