### Criteria for discontinuing interventions

*Grade 2 toxicities:* For grade 2 toxicities, the patient will be followed more carefully, with additional laboratory and/or clinic visits as necessary, and the study drugs temporarily held at the investigator's discretion.

*Grade 3 toxicities:* For any grade 3 toxicity that in the investigator’s judgment is due to study drug(s), the causative study drug(s) will be held. The clinician will rule out other possible causes of the symptoms before discontinuing study medication. When possible, concomitant medications will be held first at the discretion of the investigator if he/she suspects they are contributing to the toxicity. Depending on the nature and severity of the toxicity, the degree to which it resolves, and/or the emergence of alternative explanations for the toxicity or the participant’s deterioration, the study drugs(s) may be restarted at the discretion of the investigator.

*Grade 4 toxicities:* Study drug will be permanently discontinued in any participant with grade 4 renal, hepatic, cardiac, or hematological toxicity.

For all toxicities that are treatment-emergent and require the study therapy to be temporarily or permanently discontinued, relevant clinical and laboratory tests will be obtained as clinically indicated and repeated as needed until final resolution or stabilization of the toxicity.

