### Data analysis

Participants who have completed 80% of the prescribed treatment will be considered for per protocol (PP) analysis and all the patients who were randomized will be taken for intention-to-treat analysis. Modified intent-to-treat (mITT) will be performed after excluding: (a) patients with DR TBM detected after randomization; (b) diagnosed to have any other meningitis such as bacterial, viral, and fungal after randomization; (c) patients refused to be part of the trial when the initial consent was obtained from legally authorized representative; and (d) receiving less than 2 months of administration of the randomized study drugs for reasons other than death.

An interim analysis is planned at two time points during the study period, viz. after 33% and 66% of the enrolled patients have completed 8-week treatment. In addition, the interim analysis may be done if the frequency of reported serious adverse events is greater than anticipated. Reports will be provided to the DSMB at these time points.

Baseline variables will be summarized between the groups using appropriate summary statistics based on the level of measurement. The time to composite outcome will be estimated using Kaplan–Meier survival estimate and it will be compared between the three arms using Log rank test. The factors associated with time to death or disability will be assessed using Cox proportional hazards regression analysis. This is a superiority trial and we will perform two-sided tests and use type I error alpha value of 5% to claim superiority between two groups.

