## Discussion

Our trial is one of the attempts to reduce the high morbidity and mortality associated with TBM. High-dose rifampicin has been proved to be efficacious in patients with pulmonary TB. A meta-analysis of eight studies reporting on higher doses of R (13 to 35 mg/kg) in patients with pulmonary TB demonstrated accentuated sputum culture conversion as compared to the standard-dose group. The authors also reported no increased adverse events in the high dose rifampicin group [24]. Rifampicin in the current dosages and ethambutol used in the current regimen for the management of TBM have limited CNS penetration. In patients with TBM, high doses of rifampicin are associated with increased CSF exposure, improved clinical outcomes without increased grade III or IV adverse events [25–27].

Ruslami et al. showed a 50% reduction in mortality compared to the standard oral dose (10 mg/kg) when participants were given a higher dose of intravenous rifampicin (13 mg/kg/day) in adults with TBM in Indonesia. The trial also compared ethambutol (750 mg) with moxifloxacin (400 mg vs 800 mg). Hepatotoxicity of all grades was equally distributed across the groups [25]. Higher dose of rifampicin did not increase drug-related AEs and improved the survival of patients [25]. Dian and colleagues administered three different oral doses of rifampicin (10 mg/kg vs 20 mg/kg vs 30 mg/kg) along with isoniazid, pyrazinamide, and ethambutol and compared with standard TB regimen in adults with TBM. They also demonstrated lower incidence of 6-month mortality without increase in the incidence of grade 3 and 4 AEs [27]. High-dose intravenous and oral rifampicin were found to be safe in the trial. Adults from Uganda who were suspected of having TBM were randomized to receive high-dose oral rifampicin (PO-35, 35 mg/kg/day), intravenous rifampicin (IV-20, 20 mg/kg/day), or standard-of-care control (PO-10, rifampicin 10 mg/kg/day) along with isoniazid, pyrazinamide, and ethambutol. The composite safety endpoint did not differ between the three arms (*P* = 0.342). Rifampicin exposure in the CSF was approximately eightfold higher in the oral high dose arm (35 mg/kg) than the standard of care with no additional toxicity [28].

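### The modified intention-to-treat set drops patients whose regimen is stopped early for toxicity, together with any later death or disability

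*Protocol article*

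**What the plan says.** The Data analysis section names three sets and does not say which one leads. For the full set, "all the patients who were randomized will be taken for intention-to-treat analysis". The per-protocol set requires 80% of prescribed treatment. The mITT set has four exclusions. The first three concern drug resistance found after randomization, another meningitis, and refusal after a representative's consent. The fourth, (d), is "receiving less than 2 months of administration of the randomized study drugs for reasons other than death".

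Under Criteria for discontinuing interventions, "Study drug will be permanently discontinued in any participant with grade 4 renal, hepatic, cardiac, or hematological toxicity". No time limit is attached, so the first two months are covered. For grade 3 toxicity judged to be drug-related, "the causative study drug(s) will be held", and restarting is at the investigator's discretion.

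In the first two months, arms 1 and 2 receive rifampicin 25 mg/kg and moxifloxacin with isoniazid and pyrazinamide, and arm 1 also receives aspirin. The control arm starts with "isoniazid, rifampicin, ethambutol, and pyrazinamide followed by" a ten-month continuation phase. The Objectives section lists as a secondary aim the "safety and tolerability of high-dose rifampicin and moxifloxacin when given daily for 8 weeks". The primary outcome counts death or disability from randomization onward.

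**The concern.** Exclusions (a) to (c) concern diagnosis or consent. Exclusion (d) is different because the allocated treatment can bring it about. Death is its only exception. A patient who dies on treatment at week 4 stays in mITT. A patient whose regimen is stopped at week 4 for grade 4 liver toxicity and who dies at month 3 is removed, because the short exposure was due to toxicity and not to death. The mITT comparison is thus conditional on tolerating the very drugs that distinguish the arms.

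If the intensified arms have more early toxicity stops, and stopped patients do worse than average, mITT favours the intensified arms. It could then look better than intention-to-treat, or appear to confirm it, partly because patients harmed by the regimen were taken out.

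**Working it through.** **Inputs from the protocol (Sample size section).** Composite risk is 56% in control and 36% with the intervention, with 85% power, two-sided 5%, 112 per arm, and 124 per arm after 10% loss. The two-proportion formula with pooled variance gives 110 per arm, close to the stated 112, and 112/0.9 = 124.4, stated as 124. The plan's figures are reproduced, and the point below does not depend on the small difference.

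**Assumed inputs.** The article gives no rate of early toxicity stops and no outcome risk after a stop. Let *e* be the share of an arm whose regimen is stopped for toxicity before two months, and *q* the outcome risk in those patients. Both are assumptions, so a range is shown.

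**Formula.** With true arm risk *p*, the risk left in mITT is (p − e·q)/(1 − e).

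**No true effect (p = 0.56 in both arms, 124 randomized per arm):**

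| Stops, arm 1 vs arm 3 | q | mITT risk, arm 1 vs arm 3 | Spurious benefit for arm 1 | Chance of false significance for arm 1 |
|---|---|---|---|---|
| 3% vs 2% | 0.70 | 0.5557 vs 0.5571 | 0.1 points | 2.6% |
| 5% vs 2% | 0.80 | 0.5474 vs 0.5551 | 0.8 points | 3.3% |
| 10% vs 5% | 0.80 | 0.5333 vs 0.5474 | 1.4 points | 4.0% |
| 15% vs 5% (extreme bound) | 1.00 | 0.4824 vs 0.5368 | 5.4 points | 12.5% |

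Second row, worked: (0.56 − 0.05 × 0.8)/0.95 = 0.5474 and (0.56 − 0.02 × 0.8)/0.98 = 0.5551.

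The last column is the one-directional probability, nominal 2.5%, from a two-proportion z test with 124(1 − e) patients per arm. That test follows the Sample size section and approximates the planned log-rank test. Two-sided error in the first three rows is 5.0%, 5.2% and 5.5%. Patients excluded are about 4 vs 2, 6 vs 2, 12 vs 6, and 19 vs 6.

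**When the bias vanishes or reverses.** With equal *e* and equal *q* in both arms, or with *q* = 0.56 in both arms, the difference is zero. With 5% vs 2% stops and *q* = 0.40, the risks are 0.5684 vs 0.5633, which is 0.5 points against arm 1.

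**Planned effect true (0.36 vs 0.56).**
- Stopped patients in either arm at the control risk of 0.56, stops 5% in both arms: (0.36 − 0.05 × 0.56)/0.95 = 0.3495 vs 0.5600, a difference of 21.1 points (0.2105) instead of 20.0.
- Same risks, stops 10% vs 5%: 0.3378 vs 0.5600, a difference of 22.2 points.
- Stopped arm 1 patients keep a risk of 0.36: the difference stays at 20.0.

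**The case against.** The strongest reply is that the unselected analysis is intact. Intention-to-treat keeps everyone, grade 3 and 4 events are reported separately, and a gap between mITT and intention-to-treat would be visible. That stands, and it limits the stake. It does not settle the matter, because no set is named as primary and the per-protocol set already serves as the exposure-based analysis.

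Second, the effect is small. In the three non-extreme scenarios the shift is 0.02 to 0.21 standard errors (standard error about 6.4 to 6.6 points), and two-sided error hardly moves. This also stands. The one-directional figure is the relevant one for a false claim in favour of arm 1, but it too moves little.

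Third, the documents point away from a large imbalance: the Discussion cites high-dose rifampicin in this disease with "improved clinical outcomes without increased grade III or IV adverse events". That bears on rifampicin dose and does not settle the full combination with moxifloxacin and aspirin, whose tolerability is partly a stated objective.

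Fourth, the triggering case is narrow. Missed intensive-phase doses may be made up over as much as 15 days, so many temporary holds need not lead to exclusion. If only one drug is stopped, (d) may not apply. Both points hold, but neither rescues a patient whose whole regimen is permanently stopped.

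Fifth, the shift under the planned effect depends on stopped arm 1 patients reverting to control risk, and an exposure-based analysis is expected to differ in that way. This is fair, so the case rests mainly on the no-effect scenarios.

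**Conclusion.** The concern holds. Read with the compulsory grade 4 stopping rule, exclusion (d) conditions mITT on tolerating treatment and can discard primary events in patients harmed by it. Removal is certain only where the whole regimen is stopped.

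The likely size is modest: 0.1 to 1.4 points of spurious benefit in the non-extreme scenarios, and 5.4 points only at a deliberately extreme bound. All of these rest on assumed stop rates and risks, and on stopped patients doing worse than average and being more frequent in arm 1. Direction is not guaranteed. The intention-to-treat result is not affected. This is a cheap improvement that should be made; it is not a flaw that threatens the trial's main conclusion.

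**What to change.** In the Data analysis section, extend the exception in exclusion (d) from death alone to *death or drug toxicity*. Keep these patients in mITT with their follow-up outcomes, and state that mITT is supportive to intention-to-treat. To limit open-label judgement, count a stop as toxicity when a DAIDS grade 3 or 4 event, on the grading the protocol already uses, is recorded as its reason.

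The cost is one wording change, with no extra patients, visits or procedures. The article states that recruitment has not begun, so the change cannot be suspected of being driven by outcome data.

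Two limits remain. The recorded reason rests partly on unblinded judgement: "The intervention will be administered by the site investigators who will also be treating physicians". Early stops for withdrawal, non-adherence or intolerance below grade 3 would still be excluded, which is a further reason to give intention-to-treat the lead.

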### Participant timelines and follow-up

In this assessment, demographic details, medical history, clinical examination, neurological assessment including Modified Rankin Score (MRS) and Glasgow Coma Scale (GCS), sociological assessment for compliance to trial procedures, and all other study procedures will be done. Blood will be collected for hematological (complete blood count—CBC) and biochemical tests (sugar, HbA1C, liver, and renal function tests), HBsAg, and HIV. Patients will also undergo CT or MRI imaging of the brain. We will also collect sputum for CBNAAT and AFB culture and do chest X-ray to rule out pulmonary TB. All eligible patients will be enrolled into the trial. At the time of enrolment, blood will be collected for immunological biomarkers (CRP, TNF-α, monocyte and dendritic cell functions, and other cytokines).

During the study period, patients will be followed as per the study schedule attached (Table 1). After admission to the study and treatment allocation, participants will be followed up every week for the first 2 months and monthly till the completion of the treatment. They will undergo clinical examination including detailed neurological examination and adverse event (AE) monitoring. After treatment completion, all participants will be followed up once in 3 months for a period of 12 months. Participants in the study arms I and II will complete 12 months of post-treatment follow-up at the 18th month study visit and participants in the control arm will complete their post-treatment follow-up at the 24th month study visit.

**Table 1 Tab1:** Study schedule

S No	Investigations	Pre-screening	Screening	Enrolment	W1	W2	W3	W4	W5	W6	W7	W8	M3	M4	M5	M6	M7	M8	M9	M10	M11	M12	M15	M^a^18	M21	M24
1	Screening consent		✓																							
2	Assess eligibility		✓	✓																						
3	Informed consent			✓																						
4	History and clinical examination		✓	✓	✓	✓	✓	✓	✓	✓	✓	✓	✓	✓	✓	✓	✓	✓	✓	✓	✓	✓	✓	✓	✓	✓
5	GCS		✓	✓	✓	✓	✓	✓	✓	✓	✓	✓	✓	✓	✓	✓			✓			✓	✓	✓	✓	✓
6	Modified Rankin’s score		✓	✓	✓			✓				✓		✓		✓			✓			✓	✓	✓	✓	✓
7	Sputum smear and MGIT^b^		✓																			✓		✓		
8	CSF analysis for AFB smear, MGIT, Xpert, and to rule out other etiology as appropriate	✓																								
19	CSF cytology, biochemistry,	✓																								
10	HIV		✓																							
11	Urine pregnancy test^c^		✓					✓				✓	✓	✓	✓	✓	✓	✓	✓	✓	✓	✓				
12	Hepatitis B and C		✓																							
13	LFT		✓			✓		✓		✓		✓		✓		✓			✓			✓				

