### Sample size

The trial is powered to assess the superiority of intensified regimen (arm 1) compared to control regimen (arm 3). A systematic review and meta-analysis on treatment outcomes in TBM done by Stadelman et al. reported the proportion of mortality and disability after treatment is 24% and 32%, respectively [7]. The proportion of composite outcome (death or disability) is 56%. We assume a 20% reduction of composite outcome with our intervention (i.e., from 56 to 36%). We used the formula for Z test for comparing proportion between two groups (arm 1 and arm 3). Hence, to study the impact of “Intervention” compared to “Standard care” in reducing the composite outcome (death or disability), expecting a minimum difference of 20% between intervention arm with aspirin (arm 1) and control arm (arm 3), assuming 85% power of the study, 5% level of significance, 2-sided significance test; the required sample size was 112 patients in each arm. Considering 10% lost to follow-up, the total sample size was calculated as 372 with 124 in each arm. Previous clinical trials in TBM have evaluated mortality as an outcome and considered 30% reduction [14]. Since we propose to evaluate composite outcome of death or disability, we have assumed a conservative effect size of 20% reduction. The 10% loss to follow-up is assumed based on the previous TBM trials as well as randomized controlled trials conducted at ICMR-NIRT, Chennai [20, 21].

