The analysis for the primary outcome will be stratified based on HIV status and baseline severity of the disease measured by MRC. Sensitivity analysis will also be done including only definite and probable cases of TBM. The Cox proportional regression will be summarized using hazard ratio and 95% confidence interval. Extended Cox regression will be used in lieu of proportion Cox regression if the proportional hazard assumption is violated. The AE data will be summarized using frequency and percentage and compared between the regimens using Chi-square test. In addition, count regression models will be used to compare the number of AEs between the regimens after adjusting for other variables. Maximum plasma concentration (*C*max), time for maximal concentration (*T*max), and area under the curve (AUC) will be measured and correlated with treatment outcomes and occurrence of adverse events using log binomial regression model. Influence of PK parameters on treatment outcome will be identified using multivariable regression analysis. The quality of life will be summarized using mean and standard deviation. The variable will be compared between the regimens using ANOVA or the non-parametric alternative, Kruskal–Wallis test.

We will deal the missing data using multiple imputation technique depending on the missing data mechanism.

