### Outcome measures

Our primary outcome is mortality or disability which will be measured between inclusion and month 12 and month 24, i.e., time from randomization to death or disability during the follow-up period. All-cause mortality also will be considered as an outcome in the study. Survivors will be censored at the date they were last known to be alive (i.e., date of last follow-up visit, loss to follow-up or withdrawal). All-cause mortality rate will be measured in proportion and disability will be measured by modified Rankin scale. We will classify the score as “no disability” (a score of 0), “mild to moderate disability” (score of 1–2), and “severe disability” (3–5).

Grade 3 or 4 AEs will be measured in proportion according to Division of AIDS (DAIDS) criteria at the end of 12 months [18]. The DAIDS criterion categorizes adverse events as “mild events” (grade 1), “moderate events” (grade 2), “severe events” (grade 3), and “potentially life threatening events” (grade 4). Pharmacokinetic outcome measures will be plasma concentration time-curve during the dosing interval (AUC), peak plasma concentration (*C*_max_), and CSF concentration. Time to reach maximum plasma concentration (*T*_max_) of the study drugs will be measured up to week 8. Quality of life at baseline and 6 months, 12 months, and 24 months will be assessed in mean and standard deviation using a WHO Short form-36 (SF-36) questionnaire. It is a commonly used generic health-related quality of life (QoL) instrument which consists of 36 questions measuring health in different dimensions covering physical, mental, and social well-being of the patients. SF-36 was adapted and translated into several language and its validity and reliability were already established in India in TB context [22, 23].

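### The primary analysis stratifies on HIV status and MRC grade but does not name the enrolment Rankin score, forgoing a modest and uncertain gain in precision

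*Protocol article*

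**What the plan says.** The Outcome measures section makes the primary outcome the time from randomization to death or disability, and says that "disability will be measured by modified Rankin scale". The same scale is taken at baseline: Participant timelines and follow-up lists "neurological assessment including Modified Rankin Score (MRS) and Glasgow Coma Scale (GCS") among the initial assessments, and the Modified Rankin row of Table 1 is ticked at both screening and enrolment.

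For the arm comparison, Data analysis estimates time to the composite by Kaplan–Meier and says "it will be compared between the three arms using Log rank test". It adds: "The analysis for the primary outcome will be stratified based on HIV status and baseline severity of the disease measured by MRC". No other baseline variable is named for the primary analysis. Cox regression is introduced for studying predictors of the composite event. It is to be reported as hazard ratios with 95% intervals, with an extended Cox model as fallback if hazards are not proportional. Its covariates are not listed.

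The Sample size section powers arm 1 against arm 3 with a Z test for two proportions, 56% against 36%, "assuming 85% power of the study, 5% level of significance, 2-sided significance test". No covariate enters that calculation. The Randomization section describes permuted blocks and names no stratification factor.

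**The concern.** A baseline measurement on the scale that later defines an outcome component is usually among the better predictors of that outcome. MRC grade has three levels and carries part of baseline severity. The Rankin score can add to it only to the extent that it varies, and predicts outcome, within a grade.

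If it does, a log-rank test or Cox model that omits it leaves explainable variation in the comparison, and the treatment effect is tested with less power than the collected data allow. The score already sits in the enrolment record, and the scale is next scored at weeks 1, 4 and 8. Early disability status could plausibly follow the enrolment value, although the documents do not show how closely.

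What is at stake is efficiency. Neither the validity of the test nor the stated sample size is in question.

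**Working it through.** **1. Inputs.** From Sample size: 56% against 36%, two-sided 5%, 85% power, 112 evaluable per arm (124 after 10% loss, 372 in total). Not in the documents: how well the Rankin score predicts outcome within MRC grade. That is varied below.

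**2. Reproducing the plan's figure.** With pooled variance in both terms, n = (1.960 + 1.036)² × 2 × 0.46 × 0.54 / 0.20² = 111.5, so 112 per arm. The version with pooled variance under the null only gives 110. At 112 per arm:

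- standard error under the null: √(2 × 0.46 × 0.54 / 112) = 0.0666
- standard error under the alternative: √((0.56 × 0.44 + 0.36 × 0.64) / 112) = 0.0652
- power: Φ((0.20 − 1.96 × 0.0666) / 0.0652) = Φ(1.065) = 85.6%

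The stated figure holds with no covariate.

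**3. Simple approximation.** If the Rankin score explains a share R² of the outcome variance left after the strata, the effective size is 112 / (1 − R²), and the size for unchanged power is 112 × (1 − R²).

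| Assumed R² | Power at 112 per arm | Per arm for the same power |
|---|---|---|
| 0 | 85.6% | 112 |
| 0.05 | 87.4% | 107 |
| 0.10 | 89.1% | 101 |
| 0.20 | 92.3% | 90 |

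**4. Simulation of the planned type of analysis.** Cox models stratified by MRC grade, with and without the Rankin score as a linear term; 2,000 trials per row, 112 per arm, risks calibrated to 56% and 36%. Assumptions:

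- MRC grades in proportions 30/50/20%, hazard ratio about 1.65 per grade
- within-grade Rankin deviation scored −2 to +2
- exponential event times
- HIV ignored

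Monte Carlo error is about 0.7 points for each power figure.

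| Assumed HR per Rankin point within grade | Stratified by MRC | Plus Rankin | Difference (points) |
|---|---|---|---|
| 1.00 | 87.4% | 87.1% | −0.3 (noise) |
| 1.22 | 87.8% | 89.0% | +1.2 |
| 1.49 | 88.6% | 90.7% | +2.1 |
| 1.82 | 89.1% | 94.3% | +5.2 |
| 2.23 | 89.6% | 96.3% | +6.7 |

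As a cross-check on level, constant hazards give a hazard ratio of ln 0.64 / ln 0.44 = 0.544 and 112 × (0.56 + 0.36) = 103 events. Schoenfeld power is then 87.2%, close to the first row.

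**5. Second simulation, binary composite.** Logistic model with MRC grade, with and without a 0–5 baseline Rankin score; 2,000 trials. At within-grade correlations of 0.24, 0.32, 0.40 and 0.48, power goes from 88.9 to 90.7%, 89.0 to 92.3%, 89.7 to 93.8%, and 88.3 to 95.0%. The gains are 1.8, 3.3, 4.1 and 6.7 points. Linear interpolation puts a 5-point gain at a correlation of about 0.43. Type I error with the score added was 5.6%; the Monte Carlo standard error there is √(0.05 × 0.95 / 2000) = 0.5 points, so this is compatible with 5%.

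**The case against.** **The article is a condensation.** A covariate list may sit in the full protocol or analysis plan. This stands to the extent that non-mention is not proof of exclusion. A reader might infer that Cox regression is reserved for a risk-factor exercise, but the planned hazard ratios, intervals and extended Cox fallback fit estimation of a treatment effect equally well. Still, the article is not silent on conditioning: it names two variables for the primary analysis, and the Rankin score is not one of them.

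**Planned power is intact.** This stands in full. A reader might infer that the trial is underpowered without the score. The 85% was set for an unadjusted test and is met.

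**Severity is already handled by MRC grade.** This stands in part. Only what the Rankin score adds within grade counts. A tempting calculation multiplies the variance by 1 − 0.5² and moves unadjusted power (unpooled variance) from 86.5% to 94.3%, about 8 points. That compares with a test using no baseline information, which is not the plan, and it borrows a linear-model formula for a time-to-event analysis.

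**The score is a baseline value for only part of the outcome.** This stands. Deaths make up 24 of the assumed 56 points, and how well the score predicts death is not documented.

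**Chance imbalance is not bias.** This stands. With 112 per arm, the between-arm difference in a standardised covariate has SD √(2/112) = 0.134. With outcome SD about 0.49 and correlations of 0.24 to 0.48, its contribution to the risk difference has a 95% range of about 1.96 × 0.134 × 0.49 × 0.24 = ±3 points to ±6 points. A reader might infer that this distorts the primary result. It is already inside the standard error and the 5% error rate; adjustment merely removes it.

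**Conclusion.** The point holds as forgone precision. The stated primary analysis does not name a baseline measurement that is collected in every patient on the scale defining the disability component. Relative to the MRC-stratified plan, the gain from adding it ranges from nil, through about 1 to 2 points of power (hazard ratio 1.2 to 1.5 per Rankin point), to about 5 points (hazard ratio 1.8). The upper end is about 7 points, at a within-grade correlation near 0.48.

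These sizes rest on assumed prognostic strength, an assumed MRC mix and simplified event times, with HIV left out. The documents support no single value in the range. Nothing here makes the sample size wrong, the test invalid or the effect estimate biased. The change is worth making because the data exist, the cost is very small, and in the simulation nothing measurable is lost if the score proves uninformative.

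**What to change.** In Data analysis, state in advance that the arm 1 versus arm 3 effect on the primary outcome is estimated from a Cox model stratified by HIV status and MRC grade, with the enrolment modified Rankin score as a covariate in one stated form (the calculations above used a linear term). Keep the log-rank test with the same strata as supportive, and keep the extended Cox model as the planned response to non-proportional hazards. If the full protocol or analysis plan already specifies this adjustment, bring the article's description into line with it.

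The cost is one sentence; no extra visit, measurement or patient is needed. The drawback is that the hazard ratio becomes conditional on the Rankin score as well as the strata, so an adjusted absolute risk difference should be reported beside it, on the scale used for the 20-point target. Timing matters because the trial is open label: the Trial status section says recruitment had not begun, and a covariate fixed before outcome data accrue is far easier to defend than one added later.
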